#### Secondary outcome measures

The following have been pre-defined as secondary outcomes:Adherence to daily temperature measurement: based on patient self-report of foot temperature monitoring through use of daily logbookReport of an alarm sign to the nurse: frequency of alarms signs reported to the study nurse between study arms will be comparedReport of an alarm sign in the temperature-recording logbook: frequency of alarms signs reported in the patient’s logbooks between study arms will be comparedDose-response analysis of SMS and voice messages: per protocol analysisGlycated hemoglobin control targets: reduction of 1 % or more of glycated hemoglobin after 1 year of follow-up

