### Participant recruitment and selection criteria

Recruitment will be performed in the outpatient clinics of the aforementioned hospitals. Subjects will be eligible if they have a diagnosis of T2DM, are between 18 and 80 years of age, are in risk group 2 or 3 using the diabetic foot risk classification system (as specified by the International Working Group on the Diabetic Foot) [19–21], have a present dorsalis pedis pulse in both feet, have an operating cell phone or a caregiver with an operating cell phone, and have the ability to provide informed consent. Subjects will not be eligible for enrollment if they have current foot ulcers, active Charcot osteoarthropathy, severe peripheral arterial disease, or foot infection (Fig. 1).

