**Fig. 2 Fig2:**
[figure not shown]
Flow chart. Legend: description of the trial. HbA1c: Glycated Hemoglobin SMS: Short Message Service

Blood samples, to determine baseline levels of glycated hemoglobin, will be conducted at baseline, and at 6-month and at 12-month follow-up visits.

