### Periodic assessments

Participants will be encouraged to maintain regular visits with their treating physician in the outpatient clinic. Each hospital will follow their standard of care for diabetes management without restrictions. Also participants will be asked to visit the diabetes clinic every 2 months for a general checkup and lower extremity evaluation by a nurse evaluator. If the nurse identifies an ulcer or any diabetic complication in a patient, the patient will receive conventional hospital treatment. At each 2-month visit, participants will: (1) complete a questionnaire about diabetes treatment, caregiver presence, and use of insoles and/or orthopedic shoes, and (2) have their weight and blood pressure measured. Glycated hemoglobin (HbA1c) will be measured at 6 and 12 months. In addition, information from participants’ temperature-recording logbooks will be recorded.

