### Sample size

Based on previous randomized trials and reports of ulceration in high-risk patients, we expect that 8.5 % of subjects in the thermometer plus SMS treatment group will develop ulcers during the evaluation period and that 30 % of subjects in the thermometer-only group will develop foot ulcers [6, 7]. With a power of 0.9 and an alpha of 0.05, we require a sample size of 78 subjects in each group to find an absolute change of 21 %, a reduction from 30 % to 8.5 %. Anticipating a 10 % dropout rate, we plan to enroll 86 subjects in each study group.

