### Statistical analysis

The intention-to-treat principle will be performed comparing both study arms. To compare rates of ulceration between arms, we will perform an unadjusted logistic regression, specifically:$$ \mathrm{logit}\ \left(\mathrm{P}\left(\mathrm{ulcer}\right)\right) \approx \upbeta 0 + \upbeta 1.\mathrm{intervention}+\upbeta 2.\mathrm{site} $$

where a logit function of the probability (P) of having ulcer depends on β0, the constant coefficient; β1 that indicates the intervention (1 if the participant is in the intervention arm, and 0 if otherwise), and β2 that refers to the coefficient of the study site (hospital).

Ulceration is the binary outcome and the intervention is the mixed modality application of thermometer use plus mHealth (SMS and voice messages). These analyses will include all retained participants, regardless of the number of visits attended. A finding that the coefficient is significantly greater than zero signifies that the mHealth intervention strategy has a significantly positive impact on the reduction of diabetic foot ulceration rates.

Evaluation of other outcomes will be performed according to a pre-defined approach.

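### The only HbA1c outcome defined is a yes/no fall of 1% at one year, with its unit unstated, although baseline, 6- and 12-month values would support a more informative continuous analysis

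*Protocol article*

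**What the plan says.** All references are to the protocol article.

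- **Secondary outcome measures** lists HbA1c among the pre-defined secondary outcomes, under a label about control targets. The definition is a reduction of 1% "or more of glycated hemoglobin after 1 year of follow-up". It gives no continuous version and no unit for the 1%.
- **Baseline data collection** (text after Fig. 2): "Blood samples, to determine baseline levels of glycated hemoglobin, will be conducted at baseline, and at 6-month and at 12-month follow-up visits".
- **Periodic assessments** says that HbA1c "will be measured at 6 and 12 months". Table 1 gives the same two time points and no cut-off.
- **Participant recruitment and selection criteria** sets no HbA1c limit for entry. Eligibility rests on diagnosis, age, foot risk group, pulses, phone access and consent.
- **Statistical analysis** gives a model for ulceration only. For the rest: "Evaluation of other outcomes will be performed according to a pre-defined approach".
- **Sample size** is based on ulceration: "With a power of 0.9 and an alpha of 0.05, we require a sample size of 78 subjects in each group". No HbA1c SD, correlation or expected effect is given.

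**The concern.** There are three linked weaknesses in the one-line definition.

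1. **Label and unit.** A control target is normally a level to be reached, whereas the definition is a change. Someone well controlled throughout counts as a failure, and someone who falls from 12 to 11 counts as a success. The 1% is most naturally one percentage point, but the text does not say so. At an HbA1c of 8, a relative 1% would be only 0.08 points, which is a very different outcome.
2. **Dependence on entry value.** With no HbA1c floor at entry, and on the absolute reading, participants who start near target have little room to fall by a full point. The responder rate then says much about the case mix at baseline.
3. **Loss of information.** A continuous measurement taken three times is reduced to one yes/no. This lowers the chance of detecting a real difference in glycaemic control.

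At stake is the precision and readability of one secondary comparison.

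**Working it through.** **The plan's own figure first.** Inputs are 30% vs 8.5% ulceration, alpha 0.05 and power 0.90 (Sample size). The mean proportion is 0.1925 and the difference is 0.215.

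- Uncorrected: n = [1.96·√(2·0.1925·0.8075) + 1.2816·√(0.30·0.70 + 0.085·0.915)]² / 0.215² = 68.6, so 69.
- With continuity correction: (68.6/4)·[1 + √(1 + 4/(68.6·0.215))]² = 77.6, so 78.

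The stated 78 per group reproduces as a two-sided calculation with continuity correction. It is used below as the analysed number per arm.

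**HbA1c power: assumptions.** The documents give no HbA1c figures, so these are assumed: SD 1.5 to 2.0 points, baseline-to-12-month correlation ρ 0.4 to 0.7, control-arm mean change 0 or −0.3, true difference δ 0.5 or 0.8, normal distributions, and an absolute 1-point threshold.

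**Formulas**

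- SD of change = SD·√(2(1−ρ))
- ANCOVA residual SD = SD·√(1−ρ²)
- Responder probability: Φ((−1−m)/SD of change) in control, where m is the control mean change; add δ to the numerator for the intervention arm
- Power for means = Φ(δ/(s·√(2/78)) − 1.96), with s the SD of change or the ANCOVA SD; power for proportions by the usual pooled-variance formula

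**One case in full** (SD 1.5, ρ 0.5, δ 0.5, m −0.2)

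- SD of change = 1.5; ANCOVA SD = 1.5·√0.75 = 1.299.
- Responders: Φ(−0.8/1.5) = 29.7% vs Φ(−0.3/1.5) = 42.1%.
- Responder power: Φ((0.124 − 1.96·0.0768)/0.0762) = 36%.
- Change-score power: Φ(0.5/0.240 − 1.96) = 55%.
- ANCOVA power: Φ(0.5/0.208 − 1.96) = 67%.

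**Range over the assumed grid**

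| True difference | Yes/no | Change score | ANCOVA |
|---|---|---|---|
| 0.5 points | 20–54% | 30–77% | 40–83% |
| 0.8 points | 43–92% | 63–99% | 78% to over 99% |

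For 80% power, ANCOVA needs about 41–54% of the patients that the yes/no outcome needs. The order is the same in every setting. The gap in power points is smallest where power is already high: at δ 0.8, SD 1.5, ρ 0.7 and m −0.3 it is about 92% vs over 99%.

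**How much is due to baseline adjustment.** Simulating the case worked above gives about 37% for the unadjusted responder test, 41% for the responder test adjusted for baseline, 54% for the unadjusted change score and 66% for ANCOVA. Of the 29 points between first and last (66 − 37), about 12 (66 − 54) come from adjusting a continuous outcome for baseline.

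**Dependence on entry value.** Assume baseline mean 8 to 8.5, SD 1.5 to 2, ρ 0.5 to 0.7, and no mean change. For entry value b, the 12-month value has mean μ + ρ(b−μ) and SD·√(1−ρ²). With μ 8.5, SD 2 and ρ 0.5 (conditional SD 1.732):

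- b = 6: expected 7.25; P(value ≤ 5) = Φ(−2.25/1.732) = 10%.
- b = 10: expected 9.25; P(value ≤ 9) = Φ(−0.25/1.732) = 44%.

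Over the assumed settings, a fall of at least 1 point with no treatment effect occurs in about 6–16% of those entering at 6–7, against 26–50% of those entering at 9–10. With a 0.5-point effect, those entering at 6–7 reach it in about 12–25%.

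**The case against.** The strongest reply is that the article defers the analysis of secondary outcomes to an approach that is not shown. That approach may include a continuous or baseline-adjusted HbA1c analysis, and nothing in the text rules one out. This stands as far as the model is concerned: the article does not fix an unadjusted test. It does not remove the point, because the outcome definition is stated here and is only a dichotomy.

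The stakes are also small. HbA1c is not among the listed primary or secondary aims, the messages concern thermometer use and foot care, and no document supports a 0.5-point effect. With an assumed 0.2-point effect (SD 1.5, ρ 0.5), power is about 10% for the responder test and 15% for ANCOVA, so neither would settle the question. This stands too.

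A reader might infer more than the documents support:

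- **That the cut-off biases the comparison through regression to the mean.** Randomisation exposes both arms to it equally in expectation. It adds noise, and chance baseline imbalance can matter, but it is not a bias between arms.
- **That a fixed share of power, such as a third to a half, is lost.** The share depends on inputs that the documents do not give, and it shrinks for large effects.
- **That participants near target cannot respond.** Some do, even under no effect. The baseline distribution is unknown, and on a relative reading of 1% the argument falls away.
- **That the 6-month value goes unused.** The one-year definition does not use it, but Table 1 lists HbA1c at 6 and 12 months without a cut-off.

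**Conclusion.** The point holds as a modest improvement to one secondary outcome. The article's only defined HbA1c outcome is a change threshold carrying a label about targets and an unstated unit, and it is less informative than the planned data allow. The direction of the loss is the same in every setting tried. Its size rests on the assumed SD, correlation and effect, on an absolute 1-point threshold, and on comparing an unadjusted responder test with a baseline-adjusted continuous one. The dependence on entry value rests in addition on an assumed baseline distribution. The trial is neither powered on HbA1c nor decided by it, so the ulceration result and the sample size are untouched.

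**What to change.** Make 12-month HbA1c a continuous outcome and compare arms adjusted for baseline HbA1c and site. ANCOVA is enough; a mixed model for the 6- and 12-month values with the same adjustment would also give the 6-month measurement a role and match Table 1. Keep the proportion with a 1% fall as a supportive description, say whether the 1% is absolute or relative, and replace the control-targets label with one that describes a change.

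The cost is a change of wording in the protocol and analysis plan, with no added visits, samples or participants. The small downside is that the headline becomes a mean difference rather than a responder percentage, which some readers find less direct; the retained proportion covers that.

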#### Pre-specified sub-group analyses

In all participants, by (1) caregiving status, and (2) use of insoles and/or orthopedic shoes.

In the intervention arm only, by type of recipient (patient versus caregivers) of the messaging intervention.

### Sample size

Based on previous randomized trials and reports of ulceration in high-risk patients, we expect that 8.5 % of subjects in the thermometer plus SMS treatment group will develop ulcers during the evaluation period and that 30 % of subjects in the thermometer-only group will develop foot ulcers [6, 7]. With a power of 0.9 and an alpha of 0.05, we require a sample size of 78 subjects in each group to find an absolute change of 21 %, a reduction from 30 % to 8.5 %. Anticipating a 10 % dropout rate, we plan to enroll 86 subjects in each study group.

### Statistical analysis

The intention-to-treat principle will be performed comparing both study arms. To compare rates of ulceration between arms, we will perform an unadjusted logistic regression, specifically:$$ \mathrm{logit}\ \left(\mathrm{P}\left(\mathrm{ulcer}\right)\right) \approx \upbeta 0 + \upbeta 1.\mathrm{intervention}+\upbeta 2.\mathrm{site} $$

where a logit function of the probability (P) of having ulcer depends on β0, the constant coefficient; β1 that indicates the intervention (1 if the participant is in the intervention arm, and 0 if otherwise), and β2 that refers to the coefficient of the study site (hospital).

Ulceration is the binary outcome and the intervention is the mixed modality application of thermometer use plus mHealth (SMS and voice messages). These analyses will include all retained participants, regardless of the number of visits attended. A finding that the coefficient is significantly greater than zero signifies that the mHealth intervention strategy has a significantly positive impact on the reduction of diabetic foot ulceration rates.

Evaluation of other outcomes will be performed according to a pre-defined approach.

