**Fig. 1 Fig1:**
[figure not shown]
Process of screening evaluation. Legend: description of the inclusion and exclusion criteria of the study and screening process. IWGDF: International Working Group on the Diabetic Foot

Foot evaluation to place subjects into an eligible risk group will be performed using the diabetic foot risk classification system [22] as shown in Fig. 1. This evaluation includes a short questionnaire about previous history of ulceration and/or partial foot amputation, foot evaluation to detect deformities such as hallux valgus, rigid toe contractures (such as hammer or claw toes), and prominent metatarsal heads [19], and neuropathy testing using the vibration perception threshold and the Semmes-Weinstein monofilament (SWF) [22].

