### Randomization

We will follow the Consolidated Standards of Reporting Trials (CONSORT) Statement of recommendations for the reporting of randomized trials [23]. Stratification and blocking randomization, using hospital site as a single strata, will be performed to generate a random allocation sequence. Stratification by recruiting hospital site will be used to ensure that the numbers of participants are closely balanced within intervention arms.

Subjects will be randomized to one of the two intervention arms via opaque, sealed envelopes, each bearing on the outside only the name of the hospital and a code. The preparation of envelopes will be perform using an independent researcher. Physicians providing care to study participants in recruiting sites will be blinded to the study arm allocation, and randomization will occur between 1 and 6 days after baseline data collection.

Study nurses will assign study codes to each of the study participants and, independently, codes will have been randomly assigned into the intervention arm or the control group. The study coordinator will be responsible for opening the sealed envelopes and informing participants about their assigned study arm as per the random list, as well as maintaining concealment. The subjects will be instructed not to discuss their treatment group assignment with the blinded evaluator.

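### The primary model could add baseline foot-risk group (2 vs 3) at almost no cost: an improvement in precision and protection against chance imbalance, not the correction of an error

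*Protocol article*

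**What the plan says.** - **Primary model** (Statistical analysis): "we will perform an unadjusted logistic regression, specifically". The equation that follows has a constant, an intervention term and a site term. The model is therefore described as having no adjustment although it contains site.
- **Eligibility** (Participant recruitment and selection criteria): participants "are in risk group 2 or 3 using the diabetic foot risk classification system".
- **How the group is assigned** (text under Fig. 1): by a "short questionnaire about previous history of ulceration and/or partial foot amputation", an examination for deformity, and neuropathy testing. This is part of screening, so the group is known for everyone before randomisation.
- **Randomisation** (Randomization): stratified and blocked, "using hospital site as a single strata". Risk group is not a stratum.
- **Sub-groups** (Pre-specified sub-group analyses; Sub-group analysis): caregiving status, insoles or orthopaedic shoes, and, in the intervention arm, message recipient. Risk group is not listed.
- **Planning values** (Sample size): 30% of "subjects in the thermometer-only group will develop foot ulcers" and 8.5% of "subjects in the thermometer plus SMS treatment group will develop ulcers during the evaluation period". "With a power of 0.9 and an alpha of 0.05", "we require a sample size of 78 subjects in each group"; 86 per arm are to be enrolled.

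**The concern.** The trial mixes two categories of a system built to grade foot risk, and the grading draws on ulcer history. It is reasonable to expect, though the article does not show it, that the two groups ulcerate at different rates. If so, two things follow from leaving the variable out.

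First, stratifying by hospital does not balance risk group, so the arms may differ on it by chance and the primary estimate will carry that difference. With about 30 expected ulcers (78 × (0.30 + 0.085) = 30.0), an adjustment chosen after an imbalance has been seen would be open to challenge. Pre-specifying it removes that difficulty.

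Second, some power is given up. The amount depends on how strongly risk group predicts ulceration and on how large the true treatment effect is.

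The article writes the equation out in full, so this is a stated choice and not a detail left to an analysis plan.

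**Working it through.** **1. The plan's own figure.** With p1 = 0.30, p2 = 0.085, d = 0.215, mean 0.1925, two-sided alpha 0.05 and power 0.90:

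n = [1.960·√(2 × 0.1925 × 0.8075) + 1.282·√(0.30 × 0.70 + 0.085 × 0.915)]² / 0.215² = 68.6, i.e. 69.

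With continuity correction: (68.6/4) × [1 + √(1 + 4/(68.6 × 0.215))]² = 77.6, i.e. **78**. This matches the article. 78 × 1.10 = 85.8, giving the 86 enrolled. Without the correction, power at 78 per arm is 0.934.

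**2. How often risk group is imbalanced.** The SD of the difference in proportion in group 3 is √(2q(1−q)/n). The share q is assumed.

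| q | n per arm | SD | P(difference of 10 points or more) |
|---|---|---|---|
| 0.30 | 78 | 0.073 | 17% |
| 0.40 | 78 | 0.078 | 20% |
| 0.50 | 78 | 0.080 | 21% |
| 0.40 | 86 | 0.075 | 18% |

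**3. What a 10-point imbalance does to the estimate.** Under no treatment effect, with assumed risks of 15% and 45%, the shift is 0.10 × (0.45 − 0.15) = 0.03, or 3 points. At the planned rates the true difference is 21.5 points:

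| Assumed risk-group OR | Expected difference, imbalance against / in favour of the intervention | Power at 78 per arm, same order |
|---|---|---|
| 2 | 20.4–20.5 / 22.5–22.6 | 0.91 / 0.95 |
| 4 | 19.4–19.6 / 23.4–23.6 | 0.88–0.89 / 0.96–0.97 |
| 8 | 18.4–18.9 / 24.1–24.6 | 0.85–0.87 / 0.97–0.98 |

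Ranges cover 30% and 50% in group 3. The shift is about 1 point at OR 2, 2 at OR 4 and 3 at OR 8. For scale, the standard error of the difference is √((0.21 + 0.0778)/78) = 0.061, or 6.1 points.

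**4. Power at the planned effect** (simulated logistic regression, Wald test, 78 per arm):

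| Risk-group OR, share in group 3 | Site only | Site + risk group |
|---|---|---|
| 2, 50% | 0.941 | 0.945 |
| 4, 50% | 0.937 | 0.952 |
| 8, 30% | 0.944 | 0.967 |
| 8, 50% | 0.939 | 0.956 |

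If risk group does not predict ulceration, power is about 0.94 either way. A separate simulation over ORs of 2 to 8 gave gains of about 0.3 to 3 points.

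**5. Power at a smaller effect** (treatment odds ratio 0.4 against the planned 0.217, i.e. (0.085/0.915)/(0.30/0.70); 78 per arm; 3000 or 4000 trials per scenario):

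| Control risks, group 2 / 3 | Share in group 3 | Site only | Site + risk group |
|---|---|---|---|
| 15% / 52.5% (OR about 6) | 40% | 0.53–0.54 | 0.59–0.60 |
| 10% / 50% (OR 9) | 50% | 0.52 | 0.59 |
| 20% / 45% (OR about 3) | 40% | 0.60 | 0.63 |
| 10% / 30% (OR about 4) | 50% | 0.44–0.45 | 0.46–0.47 |

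Gains are about 2 to 7 points, the larger ones only where the assumed contrast is very strong.

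**6. Validity.** With no treatment effect, the Wald tests of both models rejected in about 4% to 6% of simulated trials.

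**The case against.** The strongest reply is that nothing here is wrong. The model contains the only stratification factor, so analysis follows randomisation. A baseline variable that was not a stratum may be left out without harm to the test. Chance imbalance is part of the sampling variation that the test already allows for, and a 2 to 3 point shift is at most half a standard error. **All of this stands.** A reader might infer that the primary test is biased, or that the trial falls short of its planned power without the covariate. The documents support neither: type I error holds, and power at the planning rates is about 0.94 against a target of 0.90.

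It is also fair to say that the prognostic strength of risk group is not in the article. There is one pooled rate per arm, with no rate by group and no expected split. **That stands too**, so every size given here is conditional on assumptions.

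The objection that gains of 6 to 7 points belong to an effect the trial was not planned for is correct as far as it goes. But the planning rates are cited to earlier trials that the Background describes as trials of thermometry itself. Here both arms receive thermometry and only the messages differ (Ethical issues). A smaller effect is therefore worth protecting against, and both sets of figures belong side by side.

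Finally, a supportive adjusted analysis may be planned in a document not shown. Its absence from the article is not evidence that none exists. The point concerns only the primary model, which the article does fix.

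**Conclusion.** The concern holds as a cheap improvement, not as an error. The primary model leaves out a baseline classification that every participant has and that randomisation does not balance.

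- **Imbalance:** 10 points or more in about 17% to 21% of trials at 78 per arm, shifting the risk difference by about 2 to 3 points if the risk-group odds ratio is 4 to 8, and by about 1 point if it is 2.
- **Power:** a gain of about 0 to 3 points at the planned effect and about 2 to 7 points at an odds ratio of 0.4.
- **Validity:** unaffected; the site-only result can be interpreted as it stands.

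These sizes rest on an assumed 30% to 50% of participants in group 3 and on assumed risk contrasts. If the two groups ulcerate at similar rates, the gain is close to nil. The one point that is plain from the text alone is the wording: a model with a site term should not be called unadjusted.

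**What to change.** Before unblinding, by amendment or in the analysis plan:

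1. Set the primary model to logit P(ulcer) = b0 + b1·intervention + b2·site + b3·risk group (3 vs 2), with risk group as recorded at screening.
2. Remove the word unadjusted from the description of the model.
3. Report the standardised 12-month risk difference from this model: average each participant's predicted risk under both assignments, then take the difference. The objective and sample size are stated as incidence, so this is the natural scale.
4. Keep the site-only model as a sensitivity analysis.

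The cost is one model term using data already collected, with no change to sample size or visits. The small downside is that the odds ratio becomes conditional on risk group: at a risk-group odds ratio of 4, the planned 0.217 becomes 0.194 to 0.197 for the same underlying rates. Step 3 deals with this.

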## Methods/design

### Objectives

The main objective of this study is to compare the 1-year incidence of DFU in two arms: the intervention arm, receiving thermometry and mHealth reminders; and the control arm receiving thermometry alone. Our hypothesis is that subjects receiving SMS and voice messaging reminders will have a lower incidence of DFU than subjects who do not receive reminders. Additionally, we will compare patient compliance with thermometer use in both arms with a temperature-recording logbook.

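### The rule for reading the primary analysis has the wrong sign: under the stated model a coefficient above zero means more ulcers with mHealth, not fewer

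*Protocol article*

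**What the plan says.** Everything at issue is in the protocol article, and most of it is in the Statistical analysis section.

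- **Model.** The equation is logit(P(ulcer)) on an intercept, an intervention indicator and site. The text repeats that the modelled quantity is "a logit function of the probability (P) of having ulcer depends on β0, the constant coefficient". The outcome is ulceration, so the event is the bad outcome.
- **Coding.** The intervention term is described as "β1 that indicates the intervention (1 if the participant is in the intervention arm, and 0 if otherwise".
- **Rule for reading the result.** "A finding that the coefficient is significantly greater than zero signifies that the mHealth intervention strategy has a significantly positive impact", and the sentence goes on to say that this impact is "on the reduction of diabetic foot ulceration rates".
- **Hypothesis (Objectives).** "subjects receiving SMS and voice messaging reminders will have a lower incidence of DFU than subjects who do not receive reminders".
- **Planning rates (Sample size).** 8.5% of participants with ulcers in the messaging arm and 30% in the thermometry-only arm; 78 per group for power 0.9 at alpha 0.05, raised to 86 for 10% dropout.

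**The concern.** With the ulcer as the event and the mHealth arm coded 1, the intervention coefficient is the log odds ratio of ulceration, mHealth against control. Fewer ulcers under mHealth make it negative. The article attaches the conclusion of fewer ulcers to a positive coefficient, which contradicts both its own equation and its own hypothesis.

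The sentence is the only one in the article that says how the primary result will be turned into a conclusion. Applied as written, it would declare success if messaging significantly raised the ulcer rate, and could not declare success if messaging lowered it. The published protocol is also the public record against which the result will be judged. A rule that contradicts its own model leaves the direction of the primary conclusion open to dispute, and it could be carried into analysis code or a report.

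**Working it through.** **1. Inputs.** From Sample size: control rate p₀ = 0.30, intervention rate p₁ = 0.085, power 0.9, alpha 0.05, 78 per group. From Study design: 1:1 allocation. From Statistical analysis: event = ulcer, intervention = 1, control = 0.

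**2. Reproducing the stated sample size.** The two-sided pooled formula, with mean rate (0.30 + 0.085)/2 = 0.1925 and difference 0.215, is

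n = [1.960·√(2 × 0.1925 × 0.8075) + 1.282·√(0.30 × 0.70 + 0.085 × 0.915)]² / 0.215² = (1.093 + 0.687)² / 0.0462 ≈ 68.6, that is 69.

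With the continuity correction,

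n′ = (n/4)·[1 + √(1 + 4/(n × 0.215))]² = (68.6/4) × (1 + 1.128)² ≈ 77.6, that is **78**, as stated.

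The one-sided versions give 56 without the correction and 65 with it. Dropout: 78 × 1.1 = 85.8, that is 86, as stated. The planning rates and n = 78 therefore belong together and can be used for the check.

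**3. Sign of the coefficient.** With the stated coding,

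β₁ = ln[(p₁/(1 − p₁)) / (p₀/(1 − p₀))] = ln[(0.085/0.915)/(0.30/0.70)] = ln(0.217) = **−1.53**.

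The planned benefit lies below zero. A positive β₁ requires an odds ratio above 1, meaning higher odds of ulcer with mHealth.

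**4. Standard error at 78 per arm.** The expected counts are 6.63 with and 71.37 without an ulcer under mHealth, and 23.4 with and 54.6 without under control.

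SE = √(1/6.63 + 1/71.37 + 1/23.4 + 1/54.6) = 0.475, so β₁/SE = −1.529/0.475 = −3.22.

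**5. Chance of each conclusion** (normal approximation, critical value 1.96; simulation of 4,000 trials per scenario with the stated model, including site, and no true site effect):

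| True rates (control, mHealth) | Rule as written: β₁ significantly > 0 | Corrected rule: β₁ significantly < 0 |
|---|---|---|
| 30%, 8.5% (planned benefit), normal approximation | Φ(−3.22 − 1.96) ≈ 1.1 × 10⁻⁷ | Φ(3.22 − 1.96) ≈ 0.896 |
| 30%, 8.5% (planned benefit), simulation | 0 of 4,000 | 0.942 |
| 8.5%, 30% (harm of the same size), simulation | 0.937 | 0 of 4,000 |

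Exact enumeration of the Wald test over binomial tables, without site, gives 0.937 for the corrected rule under the planned benefit. At 86 per arm the normal approximation gives 4.7 × 10⁻⁸ and 0.922, so the larger enrolment does not change the picture.

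**6. Could another reading rescue the sentence?** It would be right if the model were for the probability of no ulcer, or if control were coded 1. The section states the opposite of both. The sentence does not name β₁, but the other two terms are the constant and site, so no other coefficient can carry an intervention effect. Nor can the positive impact mean merely a positive number, because the sentence ties it to a reduction in ulceration.

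**The case against.** The strongest reply is that this is a slip of wording with little practical risk. The hypothesis asks for a lower incidence, the sample size is built on a fall from 30% to 8.5%, and the faulty sentence itself ends by speaking of a reduction. A competent analyst would see the intended direction at once. The model, the coding, the sample size and the two-sided p-value for β₁ = 0 are all untouched, so the test loses no power. The drop from about 90% to about zero describes only what happens if the sentence is followed to the letter.

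All of that is fair, and it bears on how likely misuse is. It does not make the sentence right. Nor can the error be put down to condensation or to a separate SAP: the article does not leave the rule out, it states it, and states it backwards.

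A second reply concerns sidedness. The article does not say whether alpha is one- or two-sided, and naming the direction that counts as benefit does not make a test one-sided. That is correct. The most that can be said is that, among the formulas tried, 78 appears only with a two-sided alpha of 0.05 together with a continuity correction that the article does not mention. This supports writing the two-sided level into the corrected sentence. It is not a separate defect, and the sign error does not depend on it.

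**Conclusion.** The concern holds. By the article's own equation and coding, a reduction in ulceration means a negative intervention coefficient, and the stated rule takes a positive one as evidence of a reduction. Under the planned effect (odds ratio 0.217, β₁ = −1.53), the rule as written would be met about once in 10 million trials and the corrected rule in about 90% to 94%. Under harm of the same size, the rule as written would be met in about 94%.

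These figures assume the planning rates, 78 evaluable participants per arm, a two-sided 0.05 Wald test and no site effect. The direction of the error rests on none of these; it follows from the coding alone. The finding covers the article only, since no SAP is at hand. The intended direction is clear and the slip is probably one of drafting, but because this is the stated rule for the primary outcome, it must be corrected.

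**What to change.** Replace the sentence in the Statistical analysis section with wording such as:

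> Superiority of the mHealth strategy will be concluded if β₁ is below zero (odds ratio below 1) with two-sided p < 0.05, equivalently if the 95% confidence interval for the odds ratio lies entirely below 1. A β₁ significantly above zero indicates more ulceration with mHealth.

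Name β₁ explicitly, so that it is clear which coefficient is meant. If a separate SAP exists, check that it carries the same direction, and make the correction before the primary outcome is analysed by arm. The cost is one sentence. The model, the sample size, the data collected and the conduct of the trial do not change.
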